### Assessment of variables

#### Primary and secondary outcome

The primary outcome of this RCT will be determining the level of steatosis and liver fibrosis stage by FibroScan. The major secondary outcome variables will be the measurement of serum liver function enzymes including aspartate aminotransferase (AST), alanine aminotransferase (ALT), and gamma-glutamyl transferase (GGT), and fasting blood insulin (FBI), fasting blood sugar (FBS), homeostatic model assessment for insulin resistance (HOMA-IR), quantitative insulin sensitivity check index (QUICKI), lipid profile including serum total cholesterol (TC), serum triglycerides (TG), low-density lipoprotein cholesterol (LDL_C), high-density lipoprotein cholesterol (HDL_C) and anthropometric indicators including weight, height, and waist circumference (WC).

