**Methods and analysis:**

This is a parallel randomized clinical trial conducted on 52 overweight and obese patients with NAFLD. Participants will be randomly assigned to receive either 16:8 IF (fasting from 8 P.M. to 12 P.M. the next day) or a low-calorie (55% carbohydrate- 30% fat, 15% protein) diet for 12 weeks. Anthropometric measurements, liver assessments, and metabolic evaluations will be assessed before and after the intervention. Primary outcomes include liver steatosis and fibrosis, while secondary outcomes include liver function enzymes, insulin resistance, lipid profile, and anthropometric measurements.

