### Inclusion criteria

This clinical trial will be performed on both men and women with NAFLD (Metavir-score ≤ F2 and controlled attenuation parameter (Cap) score > 263), BMI between 25 to 35 kg/m^2^, and aged from 20 to 50 years.

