### Sample size calculation

To compare the studied variables between the two groups, considering the error of 5%, the power of 80%, and the effect size of 0.8 (based on Cohen's criterion), the minimum sample size is equal to 26 people in each group and a total of 52 people will be determined.

*t tests—Means*: Difference between two independent means (two groups)

*Analysis:* A priori: Compute required sample size

*Input:* Tail(s) = Two

Effect size d = 0.80

α err prob = 0.05

Power (1-β err prob) = 0.8

Allocation ratio N2/N1 = 1

*Output*

Noncentrality parameter δ = 2.8844410

Critical t = 2.0085591

Df = 50

Sample size group 1 = 26

Sample size group 2 = 26

Total sample size = 52

Actual power = 0.8074866

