#### Assessment of hepatic fibrosis and steatosis

Steatosis and fibrosis of the liver will be assessed in study participants using transient elastography and CAP, respectively with FibroScan before and after intervention by the same gastroenterologist. FibroScan is a noninvasive diagnostic ultrasound-based device used to measure liver scarring or fibrosis. To assess liver stiffness, transient elastography with fibroscan will be performed. Patients are requested to fast for at least 2 h before the test. Patients will be laid in the dorsal decubitus position and measurements will be taken with a probe placed on the intercostal space and right lobe of the liver. FibroScan takes 10 min to complete and liver stiffness is expressed in kilopascals (kPa) [24]:F0/F1 (kPa < 7.3): No fibrosis or mild fibrosisF2 (kPa 7.3–12.5): Moderate fibrosisF3 (kPa 12.6–17.6): Severe fibrosisF4 (kPa > 17.6): Cirrhosis

Also, we will use the FibroScan device's CAP test to assess steatosis of the liver. Individuals will be classified based on CAP cutoffs as follows [25]:S0: no steatosis: CAP < 238S1: mild steatosis: 238 ≤ CAP < 260S2: moderate steatosis: 260 ≤ CAP < 293S3: severe steatosis: 293 ≤ CAP

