### Statistical analysis

Statistical data will be analyzed using SPSS software version 22. The results will be reported as mean ± standard deviation (SD). The normality of variable distributions will be checked using the Kolmogorov–Smirnov test. If a variable does not follow a normal distribution, a logarithmic transformation will be applied. The independent t-test will be used to compare the consumption of food and nutrients between the two groups, and the chi-square test will be used to compare qualitative variables between the two groups. The analyses will be performed based on the intention-to-treat (ITT) approach. Missing values will be treated according to the linear regression method. ANCOVA with adjustment with baseline values will be used to assess the effect of intervention on dependent variables. *p*-value < 0.05 will be considered statistically significant.

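### Fibrosis stage is named as a primary outcome, but the stated 80% power holds only for a continuous measure; CAP and kPa values should be named instead

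*Protocol article*

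**What the plan says.** All references are to the protocol article.

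- **Primary and secondary outcome:** "The primary outcome of this RCT will be determining the level of steatosis and liver fibrosis stage by FibroScan". The Abstract is looser: "Primary outcomes include liver steatosis and fibrosis", with no mention of stage.
- **Inclusion criteria:** "Metavir-score ≤ F2 and controlled attenuation parameter (Cap) score > 263".
- **Assessment of hepatic fibrosis and steatosis:** "liver stiffness is expressed in kilopascals (kPa". The section then cuts kPa into F0/F1 (below 7.3), F2 (7.3 to 12.5), F3 and F4, and cuts CAP into S0 to S3 at 238, 260 and 293. Its opening sentence reads "Steatosis and fibrosis of the liver will be assessed in study participants using transient elastography and CAP, respectively". The text that follows uses elastography for stiffness and CAP for steatosis.
- **Sample size calculation:** "Difference between two independent means (two groups", two-sided alpha 0.05, d = 0.80, 26 per group, actual power 0.8074866. No outcome is attached to d.
- **Statistical analysis:** the effect of the intervention on the dependent variables is tested by ANCOVA adjusted for baseline. Separately, "the chi-square test will be used to compare qualitative variables between the two groups".

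**The concern.** A stage is a category, while a t-test sample size and ANCOVA presuppose a measured value. The article never says whether the primary comparison uses the kPa and CAP readings or the classes cut from them.

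For fibrosis the choice matters a great deal. Entry at F2 or lower, with F0 and F1 merged, leaves one cut-point, 7.3 kPa, at which improvement can be seen. A patient below it is already in the best class and can only stay or worsen. A patient above it can move down one class.

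Two things are at stake. If stage is analysed, the trial has much less power than the article claims. If the scale stays open, value or class could be chosen after the results are seen.

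**Working it through.** **1. The plan's own figure.** Inputs from Sample size calculation: n = 26 per arm, d = 0.80, two-sided alpha 0.05.

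- Noncentrality = 0.80 × √(26/2) = 2.8844; df = 50; critical t = 2.00856.
- Power from the noncentral t = 0.80749, which matches the stated 0.8074866. With 25 per arm it is 0.791, so 26 is the minimum.

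The arithmetic is correct, for one continuous endpoint.

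**2. Room to move at baseline.**

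- Fibrosis: at most F2, so F0/F1 (no better class exists) or F2 (one step down).
- Steatosis: CAP > 263 lies above the S2 threshold of 260, so every patient starts at S2 or S3 and can fall two or three grades.

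**3. Power if the fibrosis class is compared.** The article gives no kPa distribution, so the control follow-up mean m and SD s are assumptions. Follow-up kPa is taken as normal in each arm, with the plan's own shift of 0.8 SD:

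- control share at or above 7.3 kPa: p0 = 1 − Φ((7.3 − m)/s)
- shifted arm: p1 = 1 − Φ((7.3 − m)/s + 0.8)

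Power is found by enumerating all pairs of binomial counts with 26 per arm (uncorrected chi-square and Fisher's exact test, p < 0.05).

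| m / s (kPa) | (7.3 − m)/s | p0 | p1 | Chi-square | Fisher |
|---|---|---|---|---|---|
| 5.5 / 1.3 | 1.385 | 8.3% | 1.4% | 12% | 1% |
| 6.0 / 1.5 | 0.867 | 19.3% | 4.8% | 39% | 20% |
| 6.5 / 2.0 | 0.400 | 34.5% | 11.5% | 54% | 38% |
| 7.0 / 1.5 | 0.200 | 42.1% | 15.9% | 58% | 44% |
| 7.3 / any | 0 | 50.0% | 21.2% | 61% | 50% |
| 7.9 / 1.5 | −0.400 | 65.5% | 34.5% | 60% | 50% |

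The last row puts the cut midway between the two arm means. Even there, 80% power would need 40 per arm. The loss comes from cutting kPa at 7.3, not from the choice of chi-square. Adjusting the class for baseline recovers something, but adjusting kPa for baseline gains at least as much.

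**4. The same question by improvement rates.** Suppose 50% versus 20% of F2 patients improve (assumed). The share improving in each arm is the F2 share times that rate:

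| F2 share at baseline | Improving | Chi-square | Fisher |
|---|---|---|---|
| 20% | 10% v 4% | 11% | 2% |
| 50% | 25% v 10% | 31% | 19% |
| 100% | 50% v 20% | 65% | 54% |

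Larger effects do better: 70% versus 20% with every patient at F2 gives 97% / 94%. Power on stage therefore depends on the F2 share and on improvement rates, and the article states neither.

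**5. Steatosis grade.** With an assumed control CAP of 290 (SD 45) and a 0.8 SD shift, simulation gives about 73% by a rank test on S0 to S3 and about 57% by an unordered chi-square, against about 81% for the t-test on CAP. With SD 40 and control means of 320 to 280, the rank test gives about 66% to 74%.

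**The case against.** The strongest reply is that the plan already means the continuous values. The sample size is for means, results are reported as mean and SD with a log transformation where needed, ANCOVA is the analysis of the intervention effect, stiffness is given in kPa, the Abstract omits stage, and a level of steatosis can naturally be read as the CAP value. It can be added that an article often leaves the analysed scale to fuller documents.

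Much of this stands, and it rules out several stronger readings that a reader might infer:

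- **That the primary outcome is committed to a chi-square test.** The chi-square clause covers qualitative variables in general and sits beside the food-intake comparison. It does not name the primary outcome.
- **That there is almost no room to improve.** This depends on the baseline F2 share, which is not given. It also concerns fibrosis only, since steatosis grade has room to fall.
- **That the 80% is wrong.** Under the continuous reading it is correct for a single endpoint at d = 0.8.
- **That the swapped pairing of measures affects conduct.** The same section puts it right a few lines later, so it is an editorial slip.

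What the reply does not remove is the word stage in the definition of the primary outcome. This is a stated endpoint that does not fit the stated power calculation, not a detail left out. If values were meant, the outcome sentence is wrong; if stage was meant, the 80% does not cover it.

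**Conclusion.** The point holds as a mismatch between the named fibrosis outcome and the scale on which the trial is powered. The 0.8075 is right for one continuous endpoint at d = 0.8 and does not carry over to fibrosis stage. At the plan's own effect size, power on the F2 versus F0/F1 class was about 12% to 61% by chi-square and 1% to 50% by Fisher's exact test. Those ranges rest on normal follow-up kPa with assumed control means of 5.5 to 7.9 kPa, without modelling the entry limit or baseline adjustment. None of these settings came near 80%. For steatosis grade the loss is moderate, to about 73% by a rank test under the assumed CAP of 290 (SD 45). The documents leave a continuous reading open, so the defect can be cured by choosing that reading explicitly.

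**What to change.** Reword the outcome section along these lines: *The primary outcomes are CAP (dB/m) and liver stiffness (kPa) at 12 weeks, both continuous, each compared between groups by ANCOVA adjusted for its own baseline value, on the log scale if needed. S and F classes are reported descriptively.* Both measures stay primary, as the article now has them.

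In Sample size calculation, state that the 80% power is per endpoint, at d = 0.8 on these continuous scales. The value of 0.8 is a generic benchmark and would still need justifying for CAP and for kPa.

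As a minor correction, change the first sentence of Assessment of hepatic fibrosis and steatosis so that steatosis is paired with CAP and fibrosis with transient elastography, as the rest of that section has it.

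The cost is wording only. The planned FibroScan readings before and after the intervention already give both values, and no patients, visits or measurements are added.

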#### Assessment of dietary intake

As mentioned above, dietary intake will be assessed using 24-h dietary recall (including one weekend day and two working days) at baseline, weeks four, eight, and twelve of the intervention. Experienced and trained professionals will collect these recalls from the participants, and the mean intake of food items during these four recalls will be calculated in grams per day. The nutrient intake of individuals will be calculated using N4 software (Nutritionist4).

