### Compliance

Participants' food intake will be recorded every week to assess how well they are adhering to their diet. Participants will complete a total of 12 food records. Patients will be requested to report their dietary intakes using home measurements to complete their daily recall. Finally, home measurements will be converted to grams using the brochure provided. Participants' total food intake will be examined using the average of all meal recalls during the intervention period. We will calculate energy intake, micronutrients, and macronutrients from dietary recalls using Nutrition IV software (First Databank, San Bruno, CA, USA) modified for Iranian meals. Text messages will be sent to patients to increase diet compliance and remind them to follow the diet.

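### Two conflicting rules for averaging dietary intake; the one that includes the baseline recall would shrink the expected between-arm difference to 0.75 of its on-diet size

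*Protocol article*

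**What the plan says.** Three sections of the protocol article bear on this point.

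- **Compliance.** "Participants' food intake will be recorded every week to assess how well they are adhering to their diet". The section continues: "Participants will complete a total of 12 food records". For the summary, "total food intake will be examined using the average of all meal recalls during the intervention period". Energy, macronutrients and micronutrients are then derived from the recalls.
- **Assessment of dietary intake.** This section presents itself as a repeat of the earlier one: "As mentioned above, dietary intake will be assessed using 24-h dietary recall". Each occasion covers three days ("including one weekend day and two working days"), and the occasions fall "at baseline, weeks four, eight, and twelve of the intervention". The summary rule is that "the mean intake of food items during these four recalls will be calculated in grams per day".
- **Statistical analysis.** "The independent t-test will be used to compare the consumption of food and nutrients between the two groups". The section does not say which of the two averages is compared. It names ANCOVA with baseline adjustment for the effect of the intervention on dependent variables, but gives intake the t-test.

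**The concern.** The two descriptions are offered as one scheme, but they differ in when intake is collected and in which period is averaged. The second difference matters for analysis. A baseline recall describes eating before the diets begin, so it says nothing about what the arms ate while on them. Averaging it with the three later recalls pulls the between-arm comparison toward zero.

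At stake is the reading of the trial. One arm eats freely within an 8-hour window and the other has a prescribed energy deficit, so any difference in liver findings will be interpreted in the light of what each arm consumed. A summary biased toward no difference makes it easier to state that intake was similar when it was not, and so to credit meal timing with an effect that partly reflects intake.

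**Working it through.** **The plan's own figure.** The article gives no figure for the intake summary. Its only related figure is the sample size: d = 0.80, two-sided alpha 0.05 and 26 per group. This reproduces exactly by the noncentral t (noncentrality 2.8844, critical t 2.0086, power 0.8075). It is not a calculation about intake.

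**Step 1: set the two rules side by side.**

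| | Compliance | Assessment of dietary intake |
|---|---|---|
| Collection | every week | baseline, weeks 4, 8, 12 |
| Count | 12 records | 4 occasions × 3 days = 12 recall days |
| Averaging window | intervention period | all four occasions, baseline included |

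The count of 12 can be matched as 4 × 3. Collection and window cannot. Under that match only 3 × 3 = 9 of the 12 days fall within the intervention, and none of it is weekly.

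**Step 2: expected difference under the four-recall mean.** Let D4, D8 and D12 be the true between-arm differences at weeks 4, 8 and 12. Take the four recalls as equally weighted and the baseline recall as made before the diets start. Randomisation then gives an expected baseline difference of 0.

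- Four-recall mean: (0 + D4 + D8 + D12)/4
- On-diet mean: (D4 + D8 + D12)/3
- Ratio: (1/4)/(1/3) = 0.75

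The ratio does not require a constant difference. Differences of (1, 1, 1) give 0.75/1 = 0.75, and (1.5, 1, 0.5) also give 0.75/1 = 0.75. A simulation with 26 per arm gave 0.750. In a single trial, chance imbalance at baseline would move the observed ratio around this value.

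**Step 3: loss on the standardised scale.** The four-recall mean also has a somewhat smaller variance, which offsets part of the loss. Assume equal variances and a common correlation ρ between recalls (ρ is not in the documents). The variance of a k-recall mean is then (1 + (k − 1)ρ)/k, in units of the single-recall variance. The ratio of standardised effects is

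0.75 × √{[(1 + 2ρ)/3] / [(1 + 3ρ)/4]}

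| ρ (assumed) | variance, 3 recalls | variance, 4 recalls | ratio | loss |
|---|---|---|---|---|
| 0 | 0.333 | 0.250 | 0.866 | 13% |
| 0.5 | 0.667 | 0.625 | 0.775 | 23% |
| 0.9 | 0.933 | 0.925 | 0.753 | 25% |

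**Step 4: the Compliance rule.** Averaging only over the intervention period gives the baseline recall no weight, so the expected difference is the on-diet difference and nothing is lost.

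**Step 5: what baseline adjustment would add.** Under the same model, the variance of the week 4/8/12 mean adjusted for baseline is (1 + 2ρ)/3 − ρ². At ρ = 0 nothing is gained. At ρ = 0.1 the variance falls from 0.400 to 0.390 (2.5%). At ρ = 0.5 it falls from 0.667 to 0.417 (37.5%).

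**The case against.** The strongest reply is that the dilution is conditional. The Compliance rule excludes baseline, and the Statistical analysis section does not say which average feeds the t-test. This stands. A reader might infer that the reported intake difference will be a quarter too small, but the article supports only that this follows if the four-recall mean is used.

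Four other inferences are tempting and should be resisted.

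- **A worked example in kcal, with 300 shown as 225.** The 300 kcal in the Intervention section is the control arm's deficit against its own requirements. It is not an expected difference between arms, and the article states none. The four-recall sentence also speaks of food items in grams, whereas the Compliance section mentions energy directly after its intervention-period average.
- **That recorded intake is the only check that the diets differed.** Weight, BMI and waist circumference are measured before and after, and a telephone interview includes an assessment of diet. Mean daily intake does not test the eating window under either rule.
- **A specific loss of power.** The trial is not powered on intake, and any power figure needs an assumed effect and an assumed correlation.
- **That the unadjusted t-test is an error.** Applied to on-diet intake in randomised arms it is unbiased, and intake is not a listed outcome. Adjustment is a gain in precision that can be close to nil when the correlation is low.

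The possible 4 × 3 explanation of the 12 records is also fair, but it leaves weekly collection and the averaging window unreconciled. None of these replies defends averaging a pre-diet recall into a measure of on-diet intake.

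**Conclusion.** The point holds in conditional form. The two sections contradict each other on schedule and averaging window, and the article does not say which summary enters the between-arm test. This is a conflict between two stated rules, not detail left to a fuller document.

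If the four-recall mean is used, the expected between-arm difference is 0.75 of the on-diet difference. That factor rests only on equal weighting, a baseline recall made before the diets, and randomisation. The standardised loss of about 13% to 25% rests in addition on the equal-variance, common-correlation model and an assumed correlation of 0 to 0.9. If the Compliance rule is used, there is no dilution.

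The effect is confined to the intake comparison and its interpretation. The FibroScan outcomes, the other listed outcomes and the sample size are not affected. The correction is worth making before analysis but does not threaten the trial's main result.

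**What to change.** 1. State one collection schedule, in the same terms, in the Compliance section and in the section on assessment of dietary intake. If the 12 records are four occasions of three days, say so and remove the reference to weekly recording. If weekly records are also kept, describe them as a separate source.
2. Define on-diet intake as the mean of on-intervention recalls only (weeks 4, 8 and 12, or the weekly records), and report baseline intake separately by arm.
3. In the Statistical analysis section, name this summary as the one compared between arms, and use the baseline recall as a covariate, as the section already does for dependent variables. If the weekly scheme is the one retained, keep the baseline recall alongside it for this purpose.

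The cost is a few sentences and one changed analysis line. The baseline recall is already planned, so no new data are needed, and nothing in the diets themselves changes.

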#### Assessment of hepatic fibrosis and steatosis

Steatosis and fibrosis of the liver will be assessed in study participants using transient elastography and CAP, respectively with FibroScan before and after intervention by the same gastroenterologist. FibroScan is a noninvasive diagnostic ultrasound-based device used to measure liver scarring or fibrosis. To assess liver stiffness, transient elastography with fibroscan will be performed. Patients are requested to fast for at least 2 h before the test. Patients will be laid in the dorsal decubitus position and measurements will be taken with a probe placed on the intercostal space and right lobe of the liver. FibroScan takes 10 min to complete and liver stiffness is expressed in kilopascals (kPa) [24]:F0/F1 (kPa < 7.3): No fibrosis or mild fibrosisF2 (kPa 7.3–12.5): Moderate fibrosisF3 (kPa 12.6–17.6): Severe fibrosisF4 (kPa > 17.6): Cirrhosis

Also, we will use the FibroScan device's CAP test to assess steatosis of the liver. Individuals will be classified based on CAP cutoffs as follows [25]:S0: no steatosis: CAP < 238S1: mild steatosis: 238 ≤ CAP < 260S2: moderate steatosis: 260 ≤ CAP < 293S3: severe steatosis: 293 ≤ CAP

#### Biochemical assessments

Biochemical factors will be assessed in the TUMS nutrition faculty laboratory. To measure liver enzyme levels (ALT, AST, and GGT), blood glucose, and serum lipids (including TC, serum TG, and HDL_C), a 10 mL sample of venous blood will be collected after 10–12 h fast. After 30 min in the laboratory environment to clot the blood, it will be centrifuged at 3000 rpm for 10 min to extract serum. ALT, AST enzyme levels, and serum lipid profile, including TC, HDL-C, LDL-C, and serum TG, will be measured using commercial kits and enzymatic methods (Pars Azmoon kit, Tehran, Iran). The GGT level will also be measured using the International Federation of Clinical Chemistry (IFCC) recommended calorimetric-kinetic method. Blood glucose will be measured using the enzymatic glucose oxidase method using a glucose-specific kit. Also, a specific kit using the ELISA method will be used to measure FBI, and HOMA-IR and QUICKI indices will be calculated based on the formula below using FBI and fasting blood glucose (FBG) measurements [26, 27]:$$\text{QUICKI}=1/\left(\log\;(\text{fasting insulin}\; \upmu\text{U}/\text{mL}\right)+\log\;\left(\text{fasting}\;\text{glucose mg}/\text{dL}\right)$$$$\text{HOMA1-IR} = \left(\text{fasting}\;\text{insulin}\;\left(\upmu\mathrm{U}/\text{L}\right)\times\text{fasting}\;\text{glucose}\;\left(\text{mmol}/\text{L}\right)\right)\!/22.5$$

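### HOMA-IR and QUICKI are one quantity on two scales but are tested as two secondary outcomes with a data-dependent scale for HOMA-IR, and both printed formulas need correction

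*Protocol article*

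**What the plan says.** All references are to the protocol article.

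- **Primary and secondary outcome.** The secondary list includes "homeostatic model assessment for insulin resistance (HOMA-IR), quantitative insulin sensitivity check index (QUICKI), lipid profile" and further variables. Fasting insulin and fasting glucose are in the same list as outcomes in their own right.
- **Biochemical assessments.** "HOMA-IR and QUICKI indices will be calculated based on the formula below using FBI and fasting blood glucose (FBG) measurements". Two formulas follow. The QUICKI formula takes insulin in µU/mL and glucose in mg/dL, and has three opening brackets and two closing ones. The HOMA-IR formula takes insulin in µU/L and glucose in mmol/L, with divisor 22.5.
- **Statistical analysis.** "ANCOVA with adjustment with baseline values will be used to assess the effect of intervention on dependent variables", with significance at p < 0.05. On scale: "If a variable does not follow a normal distribution, a logarithmic transformation will be applied". The normality check is a Kolmogorov–Smirnov test; the version, and the time points it is applied to, are not given.

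The article names neither index as the main one and does not mention that one determines the other.

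**The concern.** Two indices built from the same two laboratory values look like two pieces of evidence in a results table. Here one is an exact function of the other, so agreement between them confirms nothing beyond the first result.

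The two p-values still differ, because ANCOVA is not invariant to a change of scale. In a trial of 52, one index can fall just below 0.05 and the other just above on identical blood samples. A reader would then have two verdicts on insulin resistance, and the authors a choice of which to feature. The normality rule adds a further data-dependent step, since the scale of HOMA-IR is settled only after the data are seen. Glycaemic status is part of the aim stated in the abstract, so this is not a peripheral outcome.

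Separately, the formulas define the outcome variables. An unbalanced bracket and a wrong unit can go straight into code or into a table of means.

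**Working it through.** **1. The plan's own calculated figure.** The sample size section uses d = 0.80, two-sided α = 0.05 and power 0.80. With n = 26 per group, δ = 0.8 × √(26/2) = 2.8844, df = 50, critical t = 2.0086 and power = 0.8075. This matches the printed output (n = 25 gives 0.7915). It is not in dispute and supplies the 26 per arm used below.

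**2. The identity.** Write I for insulin in µU/mL and G for glucose in mg/dL. The conversion mg/dL = 18 × mmol/L and base-10 logs are assumed, as the article gives neither.

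- HOMA-IR = I × (G/18)/22.5 = I × G/405, because 18 × 22.5 = 405.
- QUICKI with balanced brackets = 1/(log10 I + log10 G) = 1/log10(I × G).
- Hence QUICKI = 1/log10(405 × HOMA-IR).

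Over 100,000 simulated pairs the largest difference between the two sides was about 1e-16 and the Spearman correlation was −1.0. The Pearson correlation was −0.90 with raw HOMA-IR and −0.995 with log HOMA-IR, which is why logging brings the two tests close together.

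**3. How often the two tests split at p < 0.05.** None of these inputs is in the documents: SD of log insulin 0.4–0.6, pre–post correlation about 0.6, glucose about 95 ± 8 mg/dL, log-insulin effect −0.25 (1 − e^−0.25 = 22% lower). QUICKI is left untransformed.

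| Handling of HOMA-IR | One index significant, the other not |
|---|---|
| Never logged | 12–18% |
| Logged if plain K–S rejects | 10–11% |
| Logged if Lilliefors K–S rejects | 4–5% |
| Always logged | 2–4% |

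The two middle rows depend on when the rule fires. With log-SD 0.5, and the log applied if either baseline or follow-up fails, it fires in about 23–26% of trials with the plain test and 91–93% with Lilliefors. A run in which it fired less often (5–25% and 53–84%) gave splits of 12–15% and 6–7%.

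A wider grid (log-SD 0.4 or 0.6, correlation 0.5 or 0.7, effect −0.2 or −0.3; 3,000 trials each) gave 5–20% for raw HOMA-IR and 1.4–4.8% for log HOMA-IR.

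**4. Other operating characteristics.**

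- With no effect, raw HOMA-IR or QUICKI is significant in about 6.5–7.5% of trials, against 5% for one test and 1 − 0.95² = 9.75% for two independent tests.
- When log HOMA-IR is significant, QUICKI is too in 83–99% of trials.
- No trial had both indices significant and favouring opposite arms.
- Log HOMA-IR gains about 5–8 points of power over raw HOMA-IR and 0–4 points over the plan's conditional rule.

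**5. The printed formulas.** Take I = 12 µU/mL.

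- *QUICKI.* At G = 95 the balanced formula gives 1/(1.0792 + 1.9777) = 0.327. If the bracket opened after the division sign is closed after insulin, as the formula's markup pairs it, the result is 1/1.0792 + 1.9777 = 2.904. At G = 105 the values are 0.323 and 2.948. The second reading rises with glucose, the wrong direction for a sensitivity index.
- *HOMA-IR.* At G = 98, glucose is 98/18 = 5.444 mmol/L. With insulin in µU/mL, 12 × 5.444/22.5 = 2.90. With insulin in µU/L as printed, 12,000 × 5.444/22.5 = 2,904.

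**The case against.** The strongest reply is that nothing in the article says two positive results will be treated as independent support. Both are secondary outcomes without a confirmatory claim, and listing insulin and glucose beside them makes the overlap visible. That stands: double counting is a risk of interpretation, not something the plan commits to.

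A reader might also infer that the two indices could give opposite conclusions. The documents and the arithmetic do not support this. Both rank patients identically, and no simulated trial had significant effects in opposite directions. The realistic conflict is two p-values on either side of 0.05.

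A reader might take the figure for never logging HOMA-IR as the size of the problem. That ignores the plan's own conditional log rule, which reduces the split, by an amount that depends on the test version. It does not remove the problem, because the scale still depends on the data.

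The false-positive increase is about 1.5–2.5 points. How multiplicity over the secondary outcomes is handled is commonly left to an analysis plan that is not shown, and is no part of this point.

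The bracket is very probably a typographical slip: the formula as displayed looks like one missing final parenthesis. It would be wrong to infer that QUICKI will be miscalculated; the wrong values arise only if the pairing is coded literally. Likewise, the unit error multiplies every HOMA-IR value by the same constant, so it would leave p-values unchanged and distort only the reported means.

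**Conclusion.** The point holds as a minor one. That QUICKI is an exact transform of HOMA-IR follows from the article's own formulas once brackets and units are corrected, and rests on no simulation. The plan nevertheless tests both and lets a normality test choose the scale of one.

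Under the plan's conditional rule, roughly 4–11% of trials with a moderate effect would give split verdicts, depending on the Kolmogorov–Smirnov version, and up to about 15% if the rule fires less often. Always logging HOMA-IR brings this to 2–4%. These sizes depend on the assumed insulin variability, pre–post correlation and treatment effect; the direction of the comparison did not change over the ranges tried.

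The formula errors are visible on the page and independent of those assumptions. The primary outcome, sample size and planned power are untouched.

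**What to change.** 1. Pre-specify one insulin-resistance analysis: ANCOVA of log HOMA-IR adjusted for baseline log HOMA-IR, whatever the normality test shows, reported as a ratio of geometric means with its confidence interval.
2. Show QUICKI descriptively by arm, without its own test, and state that it is a transform of HOMA-IR.
3. Print the formulas as QUICKI = 1/[log10(fasting insulin, µU/mL) + log10(fasting glucose, mg/dL)] and HOMA-IR = fasting insulin (µU/mL) × fasting glucose (mmol/L)/22.5.

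The cost is two sentences, a bracket and a unit. One fewer secondary index is tested, but its values are still reported and no information is lost. If the investigators prefer to keep both tests, the minimum is to state that they are one result on two scales, name the one that counts and fix its scale in advance.
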